# Parent training for the treatment of irritability in children and adolescents: a multisite randomized controlled, 3-parallel-group, evaluator-blinded, superiority trial

**DOI:** 10.1186/s40359-022-00984-5

**Published:** 2022-11-22

**Keywords:** Irritability, ADHD, Parental coping strategies, Developmental disorders, Non-violent resistance, Parent management training

## Abstract

**Background:**

Irritability is common in children and adolescents with Attention Deficit Hyperactivity Disorder (ADHD), Oppositional Defiant Disorder (ODD) and with anxiety/depressive disorders. Although youth irritability is linked with psychiatric morbidity, little is known regarding its non-pharmacological treatments. Developing non-pharmacological treatments for children with severe, chronic irritability is an important target for clinical research. To achieve this goal, we will test the benefits of parent-focused therapies in reducing irritability. The aim of the study is to compare Parent Management Training (PMT) and Non-Violent Resistance Training (NVR) programs with treatment-as-usual (TAU) on the improvement of irritability in children and adolescents with a baseline Parent-rated Affective Reactivity Index of 4 or higher, in the context of ADHD and other emotional and behavioural disorders. Additionally, we will assess (i) improvement of irritability at different times and according to different informants (parents, children, clinicians); (ii) improvement of parental strategies; and (iii) acceptability of the interventions, exploring possible mechanisms of the therapeutic effect.

**Methods:**

Two hundred and seventy participants between 6 and 15 years with ADHD and other emotional and behavioural disorders will be recruited and randomly assigned with their parents to the PMT, NVR, and TAU groups. PMT and NVR programs have 10 online sessions and two booster sessions at 1 and at 3 months. The primary outcome measure is the change from baseline at 3 months after completion of the program of the Clinician-rated Affective Rating Scale (CL-ARI) assessed by a blind evaluator. Secondary outcome measures include the change from baseline from those scales: the CL-ARI, the Clinical Global Impression Improvement scale, the Parenting and Familial Adjustment Scales, the Child-rated Cranky thermometers and the Parent-rated ARI. We will assess the parent’s expressed emotions and reflexivity during the online five-minute speech sample, clinical dimensions through the Child Behavior Checklist 6–18 and the Inventory of Callous Unemotional traits. Evaluations will be done remotely at baseline and at 1- and 3-months follow-up visits.

**Discussion:**

We expect a benefit in controlling irritability in the treatment groups. This will constitute an important achievement in promoting parental support programs in the treatment of irritability in the context of emotional and behavioural disorders.

Clinicaltrials.gov. Number: NCT05528926. Registered on the 2nd of September, 2022.

## Background

### Background and rationale {6a}

Irritability is defined as developmentally inappropriate proneness to anger [1]. Irritability is a symptom of several mental health conditions in children and adolescents such as attention deficit hyperactivity disorder (ADHD), oppositional defiant disorder (ODD), conduct disorder (CD), depressive disorders, and anxiety disorders. Both tonic (e.g., negative quality of mood) and phasic (e.g., temper outbursts) irritability are criteria of the Disruptive Mood Dysregulation Disorder reported in the Diagnostic and Statistical Manual of Mental Disorders (DSM–5) [2, 3].

Irritability is associated with poor functional outcomes across the lifespan [4, 5], with concurrent and longitudinal emotional disorders [6, 7], suicidality [8], and impaired academic and socio-professional functioning [5]. Children with high irritability also have distinct physiological profiles with hyper-reactivity to stress and to threat perception [9, 10].

Irritability is included in the negative valence system of Research Domain Criteria (RDoC) as “frustrative non-reward”. According to this neuroscience-based classification, irritability is an excessive response of an individual faced with the impossibility to achieve an expected goal. As such, it has been linked to dysregulations of the autonomic nervous system [11] and the reward network. Another pathophysiological line of research conceptualizes irritability as an aberrant response to threat (e.g., irritable individuals may attack more rapidly and in broader contexts) [12].

Despite the high prevalence and health issues related to irritability, there is little treatment research on this topic. Developing evidence-based non-pharmacological treatment options for children suffering from severe, chronic irritability is therefore a particularly important target for clinical research. One of the first steps in achieving this goal includes testing new therapies against extant interventions. Parent training programs decrease aggressive behaviors in children [13] and are therefore good candidates for the improvement of irritability. Low parental warmth, lack of positive parental emotion socialization, and high parental expressed emotions have been linked with irritability in children [14, 15] and could therefore be targeted in parental programs.

Research on the biological and psychological mechanisms mediating irritability is also needed to further improve the specificity of therapeutic actions [16].

### Parent management training (PMT)

Parent Management Training (PMT) is the gold-standard treatment for disruptive behavior disorders in children and adolescents. Barkley’s program is a PMT specifically designed for parents of defiant children [17, 18]. It can be performed either in a group (involving 6–8 families) or on an individual basis (one family). Generally, the program consists of 10–12 bi-monthly, 90-min training sessions. The objective is to train parents to cope with the child’s behavioural difficulties by teaching them effective control strategies that are coherent and adapted to the “deviant” behavior of their children; this reduces the intensity and the repercussions of undesirable behavioural events within the family. Numerous studies have demonstrated the efficacy of Barkley’s program. Following group training, parents report fewer behavior problems and with lower intensity [19]. The environment surrounding children with behavioural or emotional disorders must be as structured as possible. Disorganized, chaotic, and unpredictable environments can aggravate symptoms and favor the development of comorbidities. Hence, the importance of starting care via parental training can assure a good adjustment between the family environment and the special needs of the patient [20]. A Cochrane review involving 284 children (ages 5 to 18) found that parental guidance programs seemed to improve child behavior and reduce parental stress [13].

### Non-violent resistance (NVR)

The NVR psychological therapeutic model was developed by Pr. [name] from the University of Tel Aviv to help parents cope with their child's violent and risky behaviors [21, 22]. Along with increasing parental presence and adherence to clear rules, the program’s core features are parental self-control and emotional support. In the NVR program, parents recruit supporters to help them dealing with their children’s problematic behaviors. Developing emotional control means the parent opposes non-violent resistance to the child's behavior, without escalating into an explosive situation. Several studies have demonstrated the efficacy of NVR across a variety of social and cultural settings (for review see [23]). NVR was shown to be effective at reducing violence and other externalizing symptoms, as well as parent–child escalation and parental helplessness. NVR treatment also helped parents to increase their positive attitudes toward the child, even in situations where parent–child interactions had become unattainable because of chronic conflict. The intervention showed high levels of feasibility and acceptability, and parents were very satisfied. Related to NVR is the concept of vigilant care [24]. This concept was developed in response to criticisms of parental monitoring, which, in some cases, has been found to lead to negative consequences such as increased parent–child conflict and excessive parental control. Vigilant care emphasizes the gradations of parental vigilance, from open attention through focused attention to active protection. In this way, parents move between different levels of involvement in response to danger signals detected from their child. Targeting parents whose children show severely disruptive behavior in the home setting [25], we aim to test both NVR and vigilant care, and to compare them to standard PMT and treatment as usual (TAU).

### Rationale

Based on the above literature, we conclude that parental skills training with PMT (which typically occurs via Barkley program in France) demonstrated various degrees of success in the treatment of disruptive behavior and emotional disorders. However, specific studies examining irritability as the main efficacy endpoint are needed.

The NVR program has specific features of particular interest for children and adolescents with severe irritability. In particular, the program outcomes include parental non-violent resistance and emotional regulation in responding to the child’s behavior. That is, the specific communication skills and techniques trained with the parents are usable in situations where the child or adolescent is involved in severe disruptive behavior and emotional distress.

Our team has developed a group format of the parent program based on Non-Violent Resistance and Vigilant Care through a collaboration with [name]. This NVR program has already been used in children with predominantly intra-familial ODD/CD in pilot clinical groups and in research settings and has shown excellent acceptability and positive feedback from participants.

Our goal is to rigorously test the NVR program in a group-format and against the most common comparator therapy in France, Barkley parental skills training program (PMT), and treatment as usual (TAU). We hypothesize that both the NVR and PMT programs will show therapeutic benefits on irritability in comparison with TAU. As this project will take place in the context of SARS-CoV2 pandemic, the parent programs will be held in the form of 2-day webinars with rehearsal sessions. We also expect that this online format will meet the expectancies of many parents because of its accessibility. This study, called RESist against Irritability Superiority Trial (RESIST RCT) will also examine other clinically relevant endpoints, as well as safety and acceptability of both the NVR parent group-format program and the standard PMT; thus, it will provide additional data for the clinical potential relevance and implementation of these programs.

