### Objectives {7}

The main objective of this study is to assess the impact of non-violent parenting resistance training (NVR) and standard parenting management training (PMT) versus “usual treatment” (TAU) in improving irritability in children and adolescents with a baseline parent-rated affective reactivity index (P-ARI) greater than or equal to 4 in the context of ADHD, ODD, CD, mood / anxiety disorders or DMDD at 3 months after the program completion.

Main study hypothesis:

Both NVR and PMT are superior to TAU in improving irritability between baseline and 3 months after the program completion.

The secondary objectives of this study are:Assess improvement of irritability at different time-points (e.g., post completion).Assess improvement of irritability according to different informants (e.g., parents, child).Assess improvement of parental strategies.Explore putative mediators of therapeutic effect (e.g., parental expressed emotion, co-occurring disorders, personality).Assess acceptability of the interventions.

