#### NVR program

Our NVR program includes 10 online sessions and 2 booster online sessions (1 month and 3 months after completion). Sessions take place over two consecutive days.

The strategies for NVR group management are described in the manual book for clinicians:

[name], [name] “Accompagner les parents d’enfants tyranniques, un programme en 13 séances» Ed Dunod 2013.

The NVR Program differs to the standard PMT such that therapists never emphasize the behavior or reaction of the child but always the reaction of parents. During each session, the principles of Non-Violent Resistance are rehearsed: “Your child wants to prove to you that you cannot control him, but you have to show that you can control yourself, and that your behaviour does not depend on his behaviour. Your success is to control yourself and to use non-violent strategies, this is your only goal. The objective is to receive kindness from your child and not to change his / her behaviour. Of course, this is what you deeply wish, but if this may happen, it will be later … first you have to change and to persist”.

This is a crucial point, as therapists have to change the paradigm of objectives. It means for example, that when a parent is desperate because they have tried using a new strategy (like a sit-in) and must cope with a temper outburst more violent than ever, we consider the situation as a very positive occurrence, as long as parent managed to keep a non-violent attitude.

Every session is structured as follows. At the beginning, parents are invited to give feedback about what happened at home with their child during the last week, and what strategy they could use. Therapists reinforce parents to consider why they are able or not able to apply strategies. At the end, therapists present and explain a new strategy to use at home: most of the sessions are practical (e.g., write a declaration, to set up a sit-in) and some are more academic (e.g., describe the principles of NVR). Slides are used in order to clarify and to assist attention. After academic presentation, we ask to parents to react, e.g., “do you agree with our observations? Do you recognize the dynamic functioning of your family? Do you think it will be possible for you to use this strategy? What would limit you? What solutions could other parents find in this situation?” Often, when a parent feels trapped and overwhelmed, we ask for input from other parents in finding effective strategies.

First Session: Introduction.

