#### Secondary endpoints

Secondary efficacy endpoint at completion:Change from baseline to follow-up at 1 month of the program of the CL-ARI [26].

Secondary efficacy endpoints at 1 month and at 3 months follow-up:Change from baseline of the Clinical Global Impression Improvement (CGI-I) scale [27].Change from baseline in the Parenting and Familial Adjustment Scale (PAFAS) [28].Change from baseline of Parent-rated ARI (P-ARI) [29, 30] and Child-rated Cranky thermometers [31].

Exploratory efficacy endpoints and putative moderators and mediators:Initial score and change from baseline of specific Child Behavior Checklist (CBCL 6–18) (parent-rated) [32]: CBCL-internalizing, externalizing, and DP/Dysregulation short scale at 1 month (M1) and at 3 months (M3).Initial score of the personality dimensions assessed by parents (Hierarchical Personality Inventory for Children; HiPIC) [33]).Initial score and change from baseline of the parental expressed emotions and reflexivity rated with the Five-minute Speech Sample (FMSS) [34] at M3.Initial score and change from baseline in the Inventory of Callous Unemotional traits (ICU) [35].

Secondary acceptability endpoints:Observance.Acceptability (questionnaire for all parents and qualitative interview in a subsample of the ancillary RESIST-QUAL; the qualitative interview will be carried out after completion of the treatment).Discontinuation from the trial due to any cause and due to specific causes.

Other assessments:Socio-demographic and early development questionnaire.Medical history.Concomitant medications.K-SADS.Clinical Global Impression Severity (CGI-S) scale at baseline.

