### Exploratory analyses {20b}

#### Observance

The number of performed sessions will be described. The discontinuation from the trial due to any cause (or due to specific causes) will be also reported and compared between groups.

Analyses for additional subgroups are not planned in the main study.

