#### Harms {22}

Any adverse events/adverse reactions/incidents related to the usual care of the patient will be declared by a health professional to the various circuits of sanitary vigilance applicable to each product or practice concerned (vigilance of the care, pharmacovigilance, materiovigilance, hemovigilance, cosmetovigilance, etc.) in conformity with the regulations in force.

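### The Rationale promises to examine the safety of NVR and PMT, but discontinuation by cause is the only planned between-arm comparison that bears on it

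*Protocol article*

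**What the plan says.** The Rationale states that the trial will look at other clinically relevant endpoints, "as well as safety and acceptability of both the NVR parent group-format program and the standard PMT".

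What follows in the protocol article:

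- **Objectives {7}.** The secondary objectives include "Assess acceptability of the interventions". Safety is not among them.
- **Secondary endpoints.** Under "Secondary acceptability endpoints" the article lists observance, an acceptability questionnaire with interviews in a subsample, and "Discontinuation from the trial due to any cause and due to specific causes". There is no adverse-event endpoint.
- **Criteria for discontinuing {11b}.** Safety concerns are one ground for withdrawal, and reasons for withdrawal must be recorded.
- **Observance, under Exploratory analyses {20b}.** "The discontinuation from the trial due to any cause (or due to specific causes) will be also reported and compared between groups".
- **Harms {22}.** "Any adverse events/adverse reactions/incidents related to the usual care of the patient will be declared by a health professional". The destination given is outside the trial: such declarations go "to the various circuits of sanitary vigilance applicable to each product or practice concerned".
- **Efficacy analyses.** The CL-ARI is analysed as change from baseline with least-square means, with a non-parametric analysis added if normality clearly fails. The CGI-I is to be analysed by the same methods.
- **NVR program.** The article foresees that a parent who tries a new strategy "must cope with a temper outburst more violent than ever".

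**The concern.** Safety and acceptability are promised in the same clause, but only acceptability has the machinery to deliver it. The Harms section, which is where one would expect trial-level recording, describes a route to external systems. It names events linked to usual care and does not mention events arising during NVR or PMT.

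The article itself describes a situation in which a child's behaviour may become worse after a new strategy is used. This is no criticism of the clinical approach. It means that some worsening is foreseeable and should be counted in the same way in all three arms.

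As planned, worsening in a minority of children would enter only as part of a mean change. A later statement that the programmes are safe would have little behind it beyond the reasons why families left the trial.

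**Working it through.** **Plan's own figure.** The article gives no safety figure, so none can be reproduced. The efficacy sample size does reproduce. With expected changes of −2, −2 and −0.5, the variance of means is 0.5. For a one-way ANOVA with three groups and SD 3, the noncentrality is 77 × 3 × 0.5 / 3² = 12.83, which gives 90.03% power at alpha 0.05 with 77 per group. Allowing for dropout, 77 / 0.85 = 90.6, against the stated 90. This point does not touch the sample size.

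**Tracing the two promises through the article.**

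| Step | Acceptability | Safety |
|---|---|---|
| Rationale | stated | stated |
| Objectives {7} | listed | not listed |
| Endpoints {12} | own group | none; discontinuation by cause filed under acceptability |
| Table 1 | session attendance | no adverse-event row |
| Analysis | observance described; discontinuation compared | discontinuation by cause only |
| Harms {22} | not applicable | external vigilance; usual-care events named |

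**Why a mean change is a weak safety measure.** As an illustration, assume that 9 of 90 children in an arm (10%) worsen by one planning SD, that is by 3 points. The arm still reaches the planned mean of −2 if the other 81 average (90 × (−2) − 9 × 3) / 81 = −207 / 81 = −2.56. The efficacy analysis would look exactly as hoped. In addition, the Full Analysis Set requires a valid primary measurement, so a child who leaves because of harm and has no final rating is not in it.

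**What safety data could show at this size.** The event rates below are assumptions, not protocol figures.

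- Zero events in 90 children, one-sided 95% upper bound: 1 − 0.05^(1/90) = 0.033, or 3.3%.
- Marked worsening of 10% versus 5% at 77 per arm, 95% half-width: 1.96 × √(0.10 × 0.90/77 + 0.05 × 0.95/77) = 1.96 × √(0.1375/77) = 0.083, or about 8 points.
- Power of a two-arm test at 90 per arm: about 19% for 2% versus 5%, 25% for 5% versus 10%, and 61% for 5% versus 15%.

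The data would therefore support description by arm with intervals, not a comparative test.

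**The case against.** Several stronger readings are tempting and the article does not support them.

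- **A reader might infer that no harm is collected or compared by arm.** That is wrong. Withdrawal reasons are recorded, safety concerns are among the grounds, and cause-specific discontinuation is compared between groups.
- **A reader might infer that no safety conclusion is possible at all.** Also wrong. The CGI-I runs to very much worse, and it and the CL-ARI are collected in all arms at both follow-up visits. Counts of worsening can be computed; the article simply does not plan them.
- **A reader might take the Harms section to exclude programme-related events.** It contains no such restriction. It names usual-care events and is silent on the rest, and an external reporting route does not forbid recording in the trial.
- **A reader might treat safety as a formal objective.** It appears in the Rationale, but not in Objectives {7} or in the aims listed in the Abstract and Discussion.
- **A reader might treat the passage on more violent outbursts as a rule for classifying harms.** It is coaching about parental self-control, and the NVR sessions include precautions for unsafe situations.

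It can also be said that a safety set and adverse-event tables belong in the analysis plan, that Table 1 is captioned as covering primary and secondary endpoints, and that a fuller protocol exists. This has force for the tables, the analysis set and the missing row in Table 1. It does not dispose of the point. The article includes its own Harms section, and what that section states does not deliver what the Rationale promises. An analysis plan can only analyse what is collected.

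**Conclusion.** The point holds in limited form. The Rationale says the safety of both programmes will be examined. Apart from discontinuation by cause, the article provides for no adverse event to be collected or compared by arm, and the scales that could show worsening are planned only as efficacy outcomes. The promised evaluation would rest on discontinuation alone.

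This is an inexpensive improvement worth making, not a flaw in the primary analysis. The conclusion rests on the article as published; if the full protocol records adverse events in every arm, the remedy reduces to saying so in the Harms section. The size of what is at stake is modest: an upper bound of 3.3% if no event occurs among 90, and about ±8 points for the assumed 10% versus 5% at 77 per arm.

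**What to change.** 1. From data already collected, tabulate by arm at V2 (1 month) and V3 (3 months) the number rated 6 or 7 on the CGI-I and the number with a higher CL-ARI than at baseline. Show the number not assessed beside each count. Add safety-related withdrawals by arm.
2. Add one structured adverse-event question at V2 and V3, worded and asked identically in NVR, PMT and TAU, and report it by arm in the Randomized Set. Ask it after the blinded ratings are complete, or on the parent form, so that answers do not reveal the allocation to the evaluator.
3. Extend the Harms section so that it also covers events arising during the programmes and says where the trial records them.
4. Keep these summaries descriptive, with confidence intervals and no formal test.

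If none of this is wanted, remove safety from the sentence in the Rationale.

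Cost: one e-CRF item at two existing visits, one table, slightly longer visits and a minor amendment. The alternative costs one word.
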